#### Quality of life measures - child

Child and adolescent OHRQoL measures document the functional and psychosocial outcomes of oral disorders. It is generally accepted that these measures are as essential as clinical indicators when assessing the oral health of individuals or populations, making clinical decisions and evaluating dental interventions, services and programs [22]. Finding a tool for measuring oral health-related quality of life in children is complicated by the rapid changes seen as children grow [22,23]. This study includes children as they age from 7 years to 14 years. The Child Perceptions Questionnaire (CPQ), which has been validated for children 8 to 10 years old [24], and the short-form version for children 11 to 14 years old will be used [25,26]. It has been found to have acceptable internal consistency, reproducibility, criteria and construct validity when used in a dental clinic/practice population in the United Kingdom [27,28].

These measures of oral health-related quality of life will be taken at baseline (T0), after one year (T1) and after 5 years or when the child turns 14, whichever comes first (T2). Comparisons will be between groups at each time point. Consideration will be given to analyzing data between time points depending on the quality of the data gathered and the outcomes of research currently underway by other groups which will be published by the end of this study’s data collection.

#### Quality of life measures - parents

Parents, will also complete an OHRQoL questionnaire consisting of the one global rating and questions from the short-form Parental Caregivers Perceptions Questionnaire (SFPCPQ), which is the parent version of the CPQ 11–14. These measures of oral health-related quality of life will be taken at baseline (T0), after one year (T1) and after 5 years or when the child turns 14, whichever comes first (T2). Comparisons will be between groups at each time point. As with the children’s OHRQoL measures, consideration will be given to analyzing data between time points depending on the quality of the data gathered and the outcomes of research currently underway by other groups which will be published by the end of this study’s data collection.

#### Type of anesthetic

Data will be collected through the CRF on the type of anesthetic used during the extraction of FPMs (for example, whether any form of sedation or general anesthetic was used for each of the teeth extracted).

#### Orthodontic/dental review

The dentist will complete a questionnaire regarding dental and orthodontic treatment at 1 year follow-up and final follow-up to find out whether:

1. the upper FPM is still present (for participants in the intervention group);

2. the upper FPM has required dental treatment and if so, details of the treatment (for participants in the intervention group);

3. the patient had, or are they currently undergoing, any orthodontic treatment? (If yes, the type of treatment);

4. they have experienced any symptoms of temporo-mandibular joint dysfunction syndrome (jaw pain).

#### Data management and statistical methods

Anonymized cast models will be 3D scanned and process data analyzed to record the type and extent of dental treatment (including the study interventions) that the subjects have received during the period of the study. This will be entered into a GCP compliant data management system Open Clinica (https://www.OpenClinica.com), which can be exported to SPSS (Statistical Package for Social Sciences, Inc., Chicago, IL, USA) v.18 for statistical analysis. Patient satisfaction questionnaires will be entered into Open Clinica and exported to SPSS for descriptive statistical analysis.

COHQoL data will be entered into Open Clinica and exported to SPSS for quantitative analysis of differences in overall and domain scores at the three time points using Friedman test for repeated measures

For between group comparisons, data will be checked for normality of distribution and any evidence of skewness. Descriptive statistics will be prepared. Appropriate parametric or non-parametric analysis allowing for any clustering effect will be undertaken to determine statistically significant differences in the outcomes listed above between the two study groups including chi-squared and *t*-tests, if normally distributed.

The proposed analyses will investigate comparisons between the intervention group, where patients have not had compensatory removal of FPMs, and the control group where patients have had this done. Specifically, we are looking for clinically significant improvement in:

•position of second permanent molars (if erupted);

•degree of tipping of the lower second permanent molars;

•spacing between lower second premolar and second permanent molars;

•position/over-eruption of upper FPM in the intervention group;

•ABO scores;

•dental/orthodontic treatment required during the study period;

•child OHQoL scores;

•use of anesthetics.

Missing data will be analyzed by multiple imputation up to the patient’s last recorded visit.

Interim analyses will not be carried out for this study as it will not be possible to measure the primary outcome until recordings are taken at 5-year follow-up, by which time patient recruitment will be complete.

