### Participant inclusion criteria

Age: 7 to 11 years

Dental History: Able to cooperate with dental treatment Regular attender or considered likely to return for follow-up

Social History: Child and carer able to understand study documentation and give consent to participate in study

Dental condition: One or two lower FPMs requiring extraction Upper FPMs are sound or restorable/restored with good long term prognosis (that is, has or requires a single surface restoration with caries less than half-way into dentine, restoration with a simple restoration)Confirmed presence of all second premolars and all second molars

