#### Secondary outcomes

The secondary outcomes for the study are:

1. position of the upper FPMs with regard to over-eruption^a^;

2. residual spacing between the lower second permanent molar and the lower second premolar^a^;

3. American Board of Orthodontics (ABO) scores^a^;

4. type of anesthetic used during procedures^b^;

5. dental or orthodontic treatment carried out during the follow-up period^b^ ;

6. Child and Parent Oral Health-Related Quality of Life (OHRQoL) scores (child and parent questionnaires).

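### The Friedman test fixed for the child quality-of-life scores crosses a change of questionnaire and has no arm term, so it yields neither a readable time effect nor a treatment comparison

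*Protocol article*

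**What the plan says.** Quality of life is the sixth secondary outcome: "Child and Parent Oral Health-Related Quality of Life (OHRQoL) scores". Trial Objectives names it, with occlusion, as one of the two benefits under study.

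Three statements govern the analysis.

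- Data management and statistical methods states, without any condition, that the scores will be exported for "quantitative analysis of differences in overall and domain scores at the three time points using Friedman test for repeated measures".
- Quality of life measures - child says "Comparisons will be between groups at each time point", and then: "Consideration will be given to analyzing data between time points depending on the quality of the data gathered". It also ties that later analysis to outside research not yet published. The parent section says the same.
- Data management and statistical methods separately plans parametric or non-parametric tests, allowing for clustering, "to determine statistically significant differences in the outcomes listed above between the two study groups". It includes "child OHQoL scores" in its list of intervention-versus-control comparisons.

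The child instrument is described as "validated for children 8 to 10 years old [24], and the short-form version for children 11 to 14 years old will be used". The entry criterion is "Age: 7 to 11 years". The last visit is at five years after treatment or at age 14, whichever is earlier. The parent section describes a single short form.

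**The concern.** A Friedman test ranks the three visits within each child. It can be interpreted only if the three scores are on one scale. Here the instrument follows age and the children age through the boundary between the two forms, so most entry ages have scores from two instruments ranked against each other. The article gives no link between them. A significant result could mean that quality of life changed, that the form changed, or both.

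The test also does not address the trial question, which is whether the arms differ. The comparisons that do address it are described only generally. They include one at T0, and the tests named, chi-squared and *t*-tests, make no use of the baseline score. At stake is how a secondary outcome named in the trial objective will be reported.

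**Working it through.** The documents give no figure on this point, so there is nothing to reproduce. The check maps ages to forms, examines what the test can detect, and compares the sections.

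**1. Which form each child completes.** Inputs: entry age 7 to 11 (Participant inclusion criteria), visit timing (Overview), age bands (Quality of life measures - child). Assumptions: ages in completed years, the form follows age at the visit, and 7-year-olds, who are below both stated ranges, get the younger form. T1 age = entry age + 1. T2 age = min(entry age + 5, 14).

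| Entry age | Form at T0 | T1 age, form | T2 age, form |
|---|---|---|---|
| 7 | 8-10 | 8, 8-10 | 12, 11-14 |
| 8 | 8-10 | 9, 8-10 | 13, 11-14 |
| 9 | 8-10 | 10, 8-10 | 14, 11-14 |
| 10 | 8-10 | 11, 11-14 | 14, 11-14 |
| 11 | 11-14 | 12, 11-14 | 14, 11-14 |

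Only 11-year-old entrants keep one form. At T2 every child is on the 11-14 form. Between arms at one visit, forms are mixed at T0 and T1 only.

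**2. No arm term.** The Friedman statistic uses only the ranks of the visits within a child. Adding the same amount to all three of a child's scores leaves those ranks unchanged, so a constant arm difference is invisible to it. A simulation confirms this (assumed: 150 per arm, total SD about 1, within-child correlation 0.5, 1,000 runs). With a 0.5 SD arm difference at every visit and no time effect, the pooled Friedman test rejected in 6.1% of runs, close to its 5% level. A Mann-Whitney test between arms at T2 rejected in 98.6%.

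**3. Sensitivity to a change of form.** The same simulation, with no true arm or time effect and an assumed form-related shift at T2:

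| Shift (SD) | Friedman rejects | Between-arm test at T2 rejects |
|---|---|---|
| 0 | 4.8% | 5.4% |
| 0.1 | 32.7% | 4.9% |
| 0.2 | 87.9% | 4.7% |
| 0.3 | 99.8% | 5.3% |
| 0.5 | 100% | 5.1% |

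The shift was applied to every child at T2, which is the pattern for entrants aged 7 to 9. Those entering at 10 would shift at T1 and those entering at 11 not at all. The rates illustrate sensitivity and do not predict this trial's result.

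**4. The two sections side by side.** The child and parent sections treat analysis between time points as something to be considered, depending on data quality and outside research. The statistical section commits to it. Both cannot stand.

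**5. The comparisons between arms.** The Methods/Design part of the Abstract places baseline measures before treatment. A between-arm test at T0 then has no treatment effect to find. At T1 and T2, linear adjustment for baseline multiplies the outcome variance by 1 - r². With r = 0 the factor is 1 (no gain). With r = 0.5 it is 1 - 0.25 = 0.75 (25% lower). The documents do not give r, and the change of form may lower it.

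**The case against.** The strongest reply is that the Friedman test is an added description of change, not the treatment comparison, and need not carry an arm term. That is largely right. A reader might infer that quality of life has no comparison between arms. The documents do not support that: the child section, the parent section and the statistical section each plan one.

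Other stronger readings also fail.

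- *That a time effect would be mostly a change of form.* The documents give no size for the shift. Only inseparability is supported.
- *That four fifths of the children are affected.* Four of the five eligible entry ages are. The age distribution is not given.
- *That the Friedman test discards any child with a missed visit.* The plan imputes up to the last recorded visit, so a missed T1 with T2 present would be filled. Children without T2 would be lost. At the planning drop-out that is 0.25 × 400 = 100, if all of it precedes T2, but they are equally absent from an unimputed T2 comparison between arms.
- *That the parent score has the same fault.* One parent form is described.

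It is also fair that unadjusted comparisons at T1 and T2 are valid under randomization, that the mix of forms balances between arms in expectation, and that covariates are commonly left to an analysis plan. Baseline adjustment is therefore an improvement, not the repair of an invalid test. The position of 7-year-olds below the validated range affects only their T0 score and should affect both arms alike.

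The reply does not remove the core. The article commits to a within-child test across two unlinked forms and contradicts its own condition on doing so.

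**Conclusion.** The point holds in this limited form. For child scores, the Friedman test over T0, T1 and T2 gives a time result that cannot be separated from the change of questionnaire for every child entering at 7 to 10. It does not compare the arms, and it is stated unconditionally where the child section is conditional. This rests on the form following age at each visit and on 7-year-olds receiving the younger form. The size of the distortion is unknown.

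The separate comparisons between arms are sound in principle, with two weaknesses: a T0 test that is uninformative if T0 precedes treatment, and named tests that leave the baseline score unused. The precision lost through the second depends on an unstated correlation (25% of the variance if it is 0.5). This is a wording change worth making for a secondary outcome. The tipping outcome and the sample size are not affected.

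**What to change.** - Delete the Friedman test for child scores, or restrict it to visits completed on the same form. Reconcile the statistical section with the conditional wording in the two quality-of-life sections.
- Drop the between-arm test at T0 and describe baseline scores by arm instead.
- Compare arms at T1 and T2 with a model adjusted for baseline score (standardized within form for the child score), age group and site. Handle form at T1 only, by a form term with the score standardized within form, or by analysis within form. No standardization of the outcome is needed at T2, where all children are on the 11-14 form.
- Use the same model for the parent score, without a form term.
- Before using T0 as a covariate, confirm that the questionnaire is completed before treatment. The Abstract says baseline measures precede treatment, whereas Participant timeline lists the first questionnaire after the extractions.

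The cost is wording only; no new data are needed. The model is slightly more complex, and the standardized baseline and T1 child scores are less directly readable.

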## Methods/Design

### Overview

The SIXES Trial is a multicenter, two-arm parallel group randomized controlled trial using a superiority framework (see Figures 1 and 2). Measurements will be taken at one year after treatment and then again at either five years after treatment or when the patient reaches 14 years of age, whichever occurs first. The trial will be set in both primary and secondary care settings, reflecting the points of presentation and treatment of eligible patients. Figure 1 shows details of screening, recruitment, randomization and participant follow-up schedule and Figure 2 is a trial CONSORT type flow diagram [21] with projected numbers of participants throughout the trial.

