### Target sample size

The sample size calculation is based on the primary outcome of tipping of the lower molar tooth. There are no published data on which to base the calculation, therefore local audit data were used. These data indicated that tipping of the molar (a dichotomous outcome of either less than or more than 15 degrees tipping in the vertical direction) lies somewhere between 50:50 and 60:40 for good to poor outcome in a representative group. A finding of a difference in this proportion of 10 percent between the two groups, for example proportions of 50:50 and 40:60, in the two comparison groups would be deemed to be clinically significant.

Sample size calculation for a power of 0.8 and an alpha of 0.05 indicated a sample of 124 in each group if the true population proportion is 60:40, or 171 if the proportion is 50:50. It was therefore decided to set the required sample size at 150 in each group, requiring 300 in total. Allowing for a drop-out rate of 25% our target sample size is therefore 400.

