### Participant allocation

Sequence generation and randomization will be via a centrally controlled web-based GCP compliant randomization system, run by Tayside Clinical Trials Unit (TCTU). Randomization will be stratified by site. To ensure balanced assignment across critical variables, a minimization algorithm will be employed, using baseline age.

Participants will receive the intervention or the control as per randomization schedule.

Stratification will be by age, into two groups: 7 and 8 years and 9, 10, and 11 years.

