**Case report form to be completed by dentist**			
Baseline demographic information	**X**		
Dental history	**X**		
Record intervention or control arm	**X**		
Record side of treatment (right or left)	**X**		
Record stage of development of lower second molar	**X**		
Record type of anesthetic/sedation used	**X**		
Record dental treatment to remaining upper first permanent molars	**X**	**X**	**X**
Record orthodontic treatment since intervention		**X**	**X**

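### The only between-group tests named are unadjusted, with no method for the clustering allowance and no role for age or baseline molar stage; if these are prognostic, some power is lost

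*Protocol article*

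**What the plan says.** All references are to the protocol article.

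- **Allocation** (Participant allocation): "Randomization will be stratified by site". Baseline age goes into a minimization algorithm meant to balance critical variables, and the same section adds: "Stratification will be by age, into two groups: 7 and 8 years and 9, 10, and 11 years". Whether age is strictly a stratum or a minimization factor, it is used in allocation.
- **Baseline record** (Table 1, study visit schedule): "Record stage of development of lower second molar", marked at baseline only.
- **Timing of the final reading** (Overview): "either five years after treatment or when the patient reaches 14 years of age, whichever occurs first".
- **Analysis** (Data management and statistical methods): the plan is to assess "differences in the outcomes listed above between the two study groups including chi-squared and" *t*-tests, the latter where the data are normal. The same sentence opens with a commitment to suitable parametric or non-parametric methods that allow for clustering. It does not say what the clusters are or how they will be handled. Age and molar stage are not mentioned in this section.

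**The concern.** Allocation that balances site and age makes the treatment difference less variable than under simple randomization, provided those factors predict the outcome. A Pearson chi-squared or two-sample *t*-test does not use that balance. Its standard error is then too large for the design, so it rejects too rarely under the null and loses power. Molar stage is not an allocation factor. Leaving it out does not distort the type I error, but it forgoes precision if stage is prognostic.

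Age has a particular claim here. With entry at 7 to 11 years and the final reading at the earlier of five years or age 14, age at entry fixes both the follow-up time and the age at which tipping is measured.

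The clustering promise does not settle the matter. Children are randomized individually within sites, so the natural allowance is to condition on site. A reader could instead inflate the variance by a design effect, which would cost power. At stake is precision in a trial that has little to spare.

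**Working it through.** **1. The plan's own figure.** Inputs from Target sample size: "Sample size calculation for a power of 0.8 and an alpha of 0.05 indicated a sample of 124 in each group" at 60:40, or 171 at 50:50, with 150 per group adopted. The good-outcome rate "lies somewhere between 50:50 and 60:40 for good to poor outcome in a representative group". The target effect is: "A finding of a difference in this proportion of 10 percent between the two groups, for example proportions of 50:50 and 40:60". Sidedness is not stated; I take two-sided.

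n per arm = [1.96·√(2p̄(1−p̄)) + 0.8416·√(p₁(1−p₁)+p₂(1−p₂))]² / (p₁−p₂)²

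For 0.50 v 0.40, with p̄ = 0.45: [1.96×0.7036 + 0.8416×0.7000]² / 0.01 = 1.968² / 0.01 ≈ 387.3, so 388. For 0.60 v 0.50 it is also 388, and for 0.60 v 0.70 it is 356. One-sided, 0.50 v 0.40 needs 305. None gives 124 or 171. A 15-point difference (0.50 v 0.35) gives 170, close to 171. Only the dropout step reproduces: 300/0.75 = 400.

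**2. Unadjusted power at 150 per arm, 0.50 v 0.40.**

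Null SE = √(0.495/150) = 0.05745; alternative SE = √(0.49/150) = 0.05716. Power = Φ[(0.10 − 1.96×0.05745)/0.05716] = Φ(−0.220) = 41.3%.

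**3. Gain from adjustment.** Approximate the effective size as n/(1−R²), where R² is the share of outcome variance explained by the covariates. The documents give no R², so a range is shown.

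| Assumed R² | Effective n per arm | Power |
|---|---|---|
| 0 | 150 | 41.3% |
| 0.02 | 153.1 | 42.0% |
| 0.05 | 157.9 | 43.1% |
| 0.10 | 166.7 | 45.0% |
| 0.20 | 187.5 | 49.5% |
| 0.30 | 214.3 | 54.8% |

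Reaching 80% would need R² ≈ 1 − 150/388 = 0.61.

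**4. Simulation check.** 300 children, 20 sites (assumed), blocked within site and age group, 2,000 trials per setting. Chi-squared is compared with a linear-probability model adjusted for site, age and stage. Covariate strengths are assumed settings.

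| Covariate strength | Null rejection: chi-squared / adjusted | Power: chi-squared / adjusted |
|---|---|---|
| None | 5.7% / 5.35% | 43.5% / 42.25% |
| Weak | 5.05% / 5.15% | 41.1% / 41.65% |
| Moderate | 4.6% / 4.7% | 42.7% / 45.0% |
| Strong | 4.0% / 5.65% | 42.15% / 50.4% |
| Very strong | 3.1% / 5.0% | 40.7% / 55.15% |

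The Monte Carlo SE is √(0.05×0.95/2000) ≈ 0.5 points for null rejection and √(0.42×0.58/2000) ≈ 1.1 points for power. Conservatism of the chi-squared test is therefore visible only in the two strongest settings (about 2 and 4 SEs below 5%). The weak-covariate gain is within noise.

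**5. Follow-up by entry age.** Follow-up = min(5, 14 − age at entry). Entry at 7 or 8 gives five years and a reading at 12 or 13. Entry at 9 to 11 gives a reading at 14, after five years for a child just turned 9 and just over two for one almost 12.

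**6. What the clustering clause could mean.** Conditioning on site keeps or raises power. Inflating the variance by an assumed design effect of 1.5 leaves 150/1.5 = 100 effective children per arm and 29% power; a design effect of 2 leaves 75 and 23%.

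**The case against.** The best defence is the full sentence. It promises an allowance for clustering, and the word introducing the tests leaves the list open. Site is the obvious cluster, and a Cochran-Mantel-Haenszel test stratified by site is itself a chi-squared test. A reader might infer that plain tests will be used and site ignored; the article does not say that. This stands. What remains is that no method is attached to the clause and that it cannot reach age or molar stage.

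Second, covariate lists often sit in an analysis plan or full protocol, and neither is shown. That is fair for fine detail. But the article does name tests, the ones named are unadjusted, and a better use of data already collected is available at no cost.

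Third, a reader might infer that type I error is generally below nominal, or that age and follow-up length are the main source of spread. Neither is supported. The conservatism appears clearly only with strongly prognostic factors, and the documents give no prognostic strength at all.

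Fourth, a reader might suspect bias from unequal follow-up. Age is balanced between arms by design, so both arms are affected alike. The issue is efficiency.

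**Conclusion.** The point holds as a modest matter of precision and clarity. The named between-group tests are unadjusted, the clustering allowance has no method, and age and baseline molar stage have no stated role. If these factors are prognostic, which the timing rule makes plausible for age, the cost at 150 per arm and 50% v 40% is about 1 to 8 points of power for R² of 0.02 to 0.20 (42.0% to 49.5%, against 41.3%). With weak covariates the gain is negligible. The figures assume a two-sided 5% test, 300 evaluable children and the n/(1−R²) approximation.

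It would be wrong to infer that adjustment rescues the trial's power. On the protocol's own 10-point difference, 80% power needs 2×388 = 776 evaluable children, or 776/0.75 ≈ 1,035 randomized. That shortfall is a separate and larger defect.

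**What to change.** State the primary analysis as a logistic regression of favorable tipping on arm, adjusted for site, age at entry and baseline stage of the lower second molar. Handle site by a random intercept or by stratification: with up to 40 sites and 300 evaluable children there are about 300/40 = 7.5 per site, too few for a free parameter for each. Enter age as a continuous variable rather than only the two allocation groups. Report the adjusted risk difference with its 95% CI.

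Use the linear equivalent, with the same covariates, for continuous outcomes measured in both arms, such as residual space and ABO score. Upper molar over-eruption is assessed only where the upper tooth was kept, so it has no between-arm comparison to adjust. Replace the clustering clause with the chosen handling of site, and keep the chi-squared and *t*-tests as supportive analyses.

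The cost is a change of wording before the outcome data are examined. Site, age and molar stage are already collected.
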